**Methods/Design:**

A randomized controlled double blind single center clinical trial with two study arms comprising a total of 40 patients has been designed to assess the effects of a single preoperative dose of melatonin before major liver resection. Primary endpoints include the determination of safety and tolerance of the regimen as well as clinical parameters reflecting pathophysiological functions of the liver. Furthermore, data on clinical outcome (infectious and non-infectious complications) will be collected as secondary endpoints to allow a power calculation for a randomized clinical trial aiming at clinical efficacy.

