## Methods/Design

After the positive vote of the ethics committee of the Faculty of Medicine, Ruprecht-Karls University of Heidelberg, Germany, enrollment of the study subjects has been started in June 2007 in this randomized controlled double blind single center clinical trial as a pilot study on the safety and tolerance of preoperative melatonin application in patients undergoing major liver resection. Patients are considered for recruitment to the study according to inclusion and exclusion criteria (Table 1). The duration of the trial for each subject is expected to be 9 days, i.e. 1 day before operation (day -1), the day of operation (day 0) and the first 7 days following the operative procedure (postoperative days 1–7). Considering a recruitment rate up to 5 cases per month, the overall duration of the trial is expected to last approximately 8–10 months. A drop-out rate of 10% (due to non-compliance, intolerance, premature discontinuation, lost to follow-up, etc) will increase the total duration of trial to about 12 months. The actual overall duration of recruitment may vary due to the availability and consent rate of patients undergoing major liver resection.

**Table 1 T1:** Criteria of inclusion and exclusion of patients.

**Inclusion criteria**	**Exclusion criteria**
patients meeting all of the following criteria are considered for inclusion in the study:	patients with any of the following will not be included in the trial:
- scheduled for elective major partial liver resection of ≥3 liver segments for liver neoplasms	- patients <18 and >90 years
- written informed consent	- patients <50 and >120 kg
- adequate contraception is required for women with childbearing potential	- patients with severe, organ-specific disorders (e.g., liver or renal failure, acute pancreatitis)
	- patients undergoing emergency procedures
	- patients with expected intubation problems
	- pregnancy and/or lactation
	- history of hypersensitivity to the investigational product or to any drug with similar chemical structure or to any compound present in the pharmaceutical form of the investigational product
	- simultaneous participation in another clinical trial
	- mental condition rendering the subject incapable of understanding the nature, scope, and consequences of the trial
	No subject will be enrolled in this study more than once.

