Before operation demographic data, medical history, physical examination, diagnosis, therapy, as well as comorbidities and concomitant medications are documented on day -1. Furthermore, routine laboratory measurements and substrate monitoring are carried out and documented (Table 2). On the day of surgery and following intubation for general anaesthesia, 500 ml milk containing test (melatonin; Helsinn Chemicals, Biasca, Switzerland) or placebo product (microcrystalline cellulose) (50 mg/kg BW) is administered via a standard gastric tube placed right after intubation of the patient. Clinical laboratory values (including chemistry, hematology, liver laboratory tests, and cytokines) and the substrates are measured on the day of operation and daily throughout the entire postoperative study period of 6 days. Clinical outcome parameters include infectious (pneumonia, wound infection, peritonitis, urinary tract infection, sepsis) as well as non-infectious (bilioma, bile fistula, pleural effusion, bleeding, circulatory insufficiency, renal insufficiency, wound dehiscence, intestinal obstruction/ileus, pulmonary embolism) complications. Sepsis is defined as the presence of at least 2 out of the following 4 criteria: (1) temperature >38°C or <36°C, (2) tachycardia >90/min, (3) respiratory insufficiency (1 out of 3 criteria: respiratory rate >20/min, hyperventilation with PaCO2 <32 mmHg or PaO2 <70 mmHg (spontaneous breathing) or PaO2/FiO2 <175 mmHg (mechanical ventilation), and (4) leukocytosis >12/nl or leukopenia <4/nl. Renal failure is defined according to RIFLE-criteria [31]. The schedule for all study related activities and data collection is listed in Table 2.

**Table 2 T2:** Flow chart, PORTAL study

**Phase**	Pre-OP day^1^	OP day^1^	Post-OP day 1–7^1^
**Study-day**	-1	0	1–7
Medical history	X		
Physical examination	X		
Inclusion/exclusion criteria	X		
Karnowsky index	X		
Patient information	X		
Patient informed consent	X		
Concomitant medication	X		X
Documentation of surgery (OPS code)		X	

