**Safety and Tolerance**			
Adverse events (AE)		X	X
*Liver*			
Integrity: AST, AP, GGT, ALT, LDH, GSH	X	X	X
Synthesis: CE, Chol, TP, PT, PTT albumin, CRP	X	X	X
Elimination: Bilirubin	X	X	X
*Kidney*			
Crea (blood), Na, K, Ca, Cl	X	X	X
Urea-N.	X	X	X
Crea (urine) for Crea-Clearance		X	X
*Substrates, metabolites, cytokines*			
Glucose, TG, lactate, IL-6, melatonin^2^	X	X	X
*Hematology*			
Hb, Hc, Thr, Leuko, Ery	X	X	X

^1 ^sampling at the same time each day, e.g. 8:00, ^2 ^sampling before, 2 h and 4 h after melatonin application

Pre-OP, pre-operative period; OP, operation/day of operation; Post-OP, post-operative period; OPS, "Operations- und Prozedurenschlüssel" [codes for operations and procedures]; UTI, urinary tract infection; AST, aspartate amino-transferase; AP, alkaline phosphatase; GGT, γ-glutamyl transferase; ALT, alanine aminotransferase; LDH, lactate dehydrogenase; GSH, glutathione; CE, choline esterase; Chol, Cholesterol, TP, total protein; PT, prothrombin time; PTT, partial thromboplastin time, CRP, c-reactive protein, Crea, creatinine; Na, natrium; K, kalium; Ca, calcium; Cl, chloride; Urea-N, urea-nitrogen; TG, triglyceride; IL, interlukin; Hb, hemoglobin, Hc, hematocrit, Thr, thrombocyte, Leuko, leukocyte; Ery, erythrocyte.

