### Statistics and data management

All analyses will be carried out on an "intent-to-treat" basis. However, attempts will be made to analyze "per protocol" and "intent-to-treat" populations separately, when statistically appropriate. For the purpose of "per protocol" analysis, two groups of 20 eligible patients completing the protocol will be considered. Drop-out patients are not to be replaced.

The target variables of this trial include laboratory values, outcome parameters and adverse events. The target variables are measured from study day -1 to study day 7. The differences of the laboratory values between study day -1 and 7 are tested with the paired t-test or, in case of uneven distribution, the Wilcoxon-test (2-sided) for within group comparison. The Mann-Whitney U test will be used to detect differences between treatment groups. The following statistical values will be calculated when appropriate: mean, standard deviation, 95%-confidence interval of the mean, minimum, lower quartile, median, upper quartile, maximum, valid number, frequency count, and percentage. The laboratory values will be counted according to their normal ranges (below normal, normal, and above normal). SAS software (Version 8.2) will be used for analysis.

All patient data (clinical and resource use) generated during the study will be recorded on the eCRFs provided by HealthEcon AG, Basel, Switzerland. These forms are specifically designed in Microsoft Office Access (Version: 1.01) to meet the data recording requirements of the clinical study protocol. Corrections of wrong entries will be recorded automatically. In addition, for any correction of data concerning "Adverse Events" or the primary target variable the reason for the correction must be entered. All data will be entered into a central database as recorded.

All data management activities will be done according to the current Standard Operating Procedures (SOPs) of HealthEcon AG.

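### Within-arm tests of laboratory change from day -1 to day 7 reflect surgery and cannot show a melatonin effect; the between-arm test is valid but has no stated input and no baseline adjustment

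*Protocol article*

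**What the plan says.** The section Statistics and data management of the protocol article sets out two kinds of test for laboratory values.

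- **Within each arm.** The quantity is "The differences of the laboratory values between study day -1 and 7", and it is "tested with the paired t-test or, in case of uneven distribution, the Wilcoxon-test (2-sided) for within group comparison".
- **Between arms.** "The Mann-Whitney U test will be used to detect differences between treatment groups". The sentence gives no variable, no time point and no covariate.

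The section does not rank one test above the other.

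Four other places bear on the point.

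- **What happens between the two days.** Table 1 admits patients "scheduled for elective major partial liver resection of ≥3 liver segments for liver neoplasms".
- **Baseline.** Methods/Design says of day -1: "Furthermore, routine laboratory measurements and substrate monitoring are carried out and documented". Table 2 marks day -1, the day of operation and days 1–7 for items such as "Integrity: AST, AP, GGT, ALT, LDH, GSH".
- **Repeated values.** Laboratory values and substrates "are measured on the day of operation and daily throughout the entire postoperative study period of 6 days".
- **Standing of these variables.** The abstract says: "Primary endpoints include the determination of safety and tolerance of the regimen as well as clinical parameters reflecting pathophysiological functions of the liver". Objectives and endpoints puts safety and tolerance first and adds the liver parameters to them.

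**The concern.** A before-after test within one arm asks whether the values moved between day -1 and day 7. After removal of three or more liver segments, many of them will move in both arms whether or not melatonin does anything. The placebo arm is there to subtract that movement, and a test confined to one arm does not use it. Yet this is the only test in the section with its variable, time points and sidedness all stated. If p-values for the two arms are printed next to each other, some readers will compare them and take one significant arm as a sign of a drug effect.

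The second issue is efficiency. With about 20 patients per arm, a measured baseline is a cheap source of precision. The article neither says what enters the between-arm test nor names an adjustment for day -1. Since the abstract counts liver parameters among the primary endpoints, the way their arm difference is estimated matters.

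**Working it through.** **Inputs from the article.** 40 patients, allocated 1:1, so 20 per arm. Laboratory values at day -1 and day 7. Resection between the two in both arms.

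**Inputs assumed.** The article gives no alpha, power, effect size, SD or correlation for these variables, so it has no figure of its own to reproduce. Assumed here: two-sided alpha 0.05, normal data, the same SD (set to 1) at both times, and a correlation r of 0.3, 0.5 or 0.7 between day -1 and day 7.

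**Step 1: what the within-arm test picks up when melatonin does nothing.** Both arms were given the same surgical shift, with 20 per arm and 4,000 simulated trials per scenario.

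| Common shift | r | Melatonin arm significant | Exactly one arm significant |
|---|---|---|---|
| 0.5 SD | 0.3 | 44% | 50% |
| 0.5 SD | 0.5 | 56% | 50% |
| 0.5 SD | 0.7 | 78% | 34% |
| 1 SD | 0.3 | 95% | 10% |
| 1 SD | 0.5 | 99% | 2% |
| 1 SD | 0.7 | 100% | 0% |

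The melatonin arm is often significant with no drug effect at all. Over all null scenarios, including no shift, the between-arm tests (Mann-Whitney on day 7 values, Mann-Whitney on change, ANCOVA) rejected in 4.2% to 5.8% of trials, close to the nominal 5%.

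**Step 2: the last column by formula.** If each arm has within-arm power p and the arms are independent, exactly one is significant with probability 2p(1-p).

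- p = 0.5: 2 × 0.5 × 0.5 = 50%
- p = 0.8: 2 × 0.8 × 0.2 = 32%
- p = 0.9: 2 × 0.9 × 0.1 = 18%

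The rate is highest for moderate surgical shifts. It falls towards zero when the shift is so large that both arms are nearly always significant.

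**Step 3: cost of not adjusting for day -1.** With SD 1 at both times, the variances are 1 for the raw day 7 value, 2(1-r) for the change, and 1-r² for ANCOVA. Hence raw/ANCOVA = 1/(1-r²), and change/ANCOVA = 2(1-r)/(1-r²) = 2/(1+r).

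| r | raw/ANCOVA | change/ANCOVA |
|---|---|---|
| 0.3 | 1/0.91 = 1.10 | 2/1.3 = 1.54 |
| 0.5 | 1/0.75 = 1.33 | 2/1.5 = 1.33 |
| 0.7 | 1/0.51 = 1.96 | 2/1.7 = 1.18 |

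The unstated input therefore matters. Below r = 0.5 the change is noisier than the raw value, and above it the reverse holds. ANCOVA has the smallest variance of the three at each of these correlations.

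**Step 4: the same comparison with the planned rank test.** Simulated power with 20 per arm and an assumed true arm difference of 0.9 SD:

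| r | Mann-Whitney, day 7 | Mann-Whitney, change | ANCOVA |
|---|---|---|---|
| 0.3 | 78% | 63% | 82% |
| 0.5 | 77% | 76% | 88% |
| 0.7 | 77% | 93% | 97% |

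**The case against.** The strongest reply is that the plan already answers the treatment question properly. It labels the paired tests as within-group and gives the comparison of arms to a test fixed in advance, with correct type I error. A rank test is a defensible choice for skewed laboratory values in a small pilot. All of that stands, and it rules out several stronger readings that a reader might infer.

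- **That the within-arm p-values are the main analysis.** The section ranks no test.
- **That there is no valid randomised evidence, or that harm would go unseen.** The Mann-Whitney test is valid. Changes in laboratory parameters also count as adverse events, and values are to be tallied against their normal ranges.
- **That the baseline is ignored.** The input to the Mann-Whitney test is not stated. The preceding sentence speaks of differences from day -1, so the test may be meant for those, and it would then use the baseline.
- **That 50% is the trial's false-positive rate.** The 2p(1-p) figures belong to a comparison of significance between arms, and the article nowhere proposes that inference.
- **That choosing t-test or Wilcoxon by the look of the data biases the treatment comparison.** The choice affects the within-arm tests only.

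The article is also condensed, so the absence of a model or of an interval for the arm difference is not a fault in itself. The full protocol or analysis plan may supply both.

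What the reply does not remove is the affirmative choice to run significance tests within each arm on a change that surgery produces in both.

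**Conclusion.** The point holds in a limited form. The planned within-arm tests cannot show a melatonin effect, because both arms undergo major resection between the two measurements. This follows from the design and needs no assumed number. How often such tests would be significant with no drug effect depends on the size of the surgical shift, which the article does not give.

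The between-arm test is sound but underspecified. Leaving out adjustment for day -1 costs precision, not validity: 1.10 to 1.96 times the ANCOVA variance if day 7 values are compared, and 1.18 to 1.54 times if changes are compared, for correlations from 0.3 to 0.7. These ratios assume normal data and equal SDs at both times. At r = 0.3 the simulated gain over Mann-Whitney on day 7 values is small (78% to 82%), and at r = 0.7 it is large (77% to 97%).

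This is a free improvement to a 40-patient pilot and not something that must be changed for the trial to give a valid comparison.

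**What to change.** In Statistics and data management:

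1. Report within-arm laboratory changes descriptively and drop their p-values.
2. State that the between-arm comparison is the inferential one for laboratory values, at day 7, the time point the section already uses. Fit an ANCOVA with the day -1 value as covariate, on the log scale for skewed analytes. Report the melatonin/placebo ratio of geometric means (or the difference, for untransformed analytes) with its 95% confidence interval.
3. Keep the Mann-Whitney test as a sensitivity analysis and state whether it uses the day 7 value or the change.
4. When writing this, reconcile the postoperative sampling period: Methods/Design gives 6 days for the daily laboratory values, while Table 2 and the statistics section run to day 7.

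The cost is analysis wording only, with no new data and no more patients. The small downside is a modelling assumption on the log scale, which the rank test covers as a sensitivity analysis.

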## Discussion

This clinical trial particularly demonstrates how a scientific hypothesis has been developed from bench to bedside, with classical chain of investigations from early experimental research to the highest level of evidence, a randomized controlled double blind clinical trial. If previous experimental findings are confirmed by the data of this clinical trial, melatonin would improve the overall outcome after major liver resection.
